## Aims and Objectives

The overall aim of this trial is to compare the effects of different graphical cardiovascular risk presentation formats on individuals' intention to reduce risk, understanding of risk information, emotional affect and worry about future heart disease, using a web-based risk calculator.

The primary objectives of this study are:

• To assess which format leads to the greatest intention to change behaviour.

• To determine which format best facilitates understanding of risk information.

• To analyse which format alters emotional affect.

• To assess which format induces worry about future heart disease the most.

• To examine the correlational validity between intention to change behaviour, understanding of risk and worry about future heart risk. To find out if understanding results in more appropriate intentions regarding cardiovascular risk and what level of worry increases intention to change behaviour.

• To determine whether intention to change behaviour, understanding of risk, and emotional affect are mediated by a person's risk category.

The secondary objectives of this study are:

• To examine the existence of the Hawthorne effect using two control groups.

• To analyse within group changes between pre and post-intervention responses in the group who completed both questionnaires.

• To evaluate the use of the internet-provided risk formatter (process evaluation), including analysis of web-logs.

• To assess the TPB's efficacy to predict intention to change behaviour to reduce future heart risk.

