Before respondents can proceed, they will be given brief details about the study, asked to indicate their informed consent electronically and will be assessed for eligibility. The computer will then randomise the respondent into one of the four arms, ensuring allocation concealment (see Figure 1). These comprise a bar graph with pre-intervention questionnaire (control group 1), bar graph only (control group 2), pictogram (intervention group 1) or metonym (intervention group 2). Following the risk assessment, all respondents will be given their risk category (low, moderate or high) and the corresponding percentage figure (< 10%, 10-20% or > 20%). The main comparators will be the accompanying graphical risk presentation formats (bar graph, pictogram and metonym).

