**Figure 1 F1:**
[figure not shown]
**Flowchart of the RCT with intervention and control groups**.

The bar graph format to be used in the two control groups consists of vertical bar graph depicting percentages. This will be animated (growing upwards) to demonstrate the wide confidence intervals of the risk categories in the Personal Risk Score [47]. A bar graph has been chosen as it is the standard presentation format commonly used in current risk prediction tools. A pictogram of 100 hearts depicting natural frequencies will be used in intervention group 1. Research shows that these formats are better understood by patients, natural frequencies intuitively offer more insight than other formats [9,10] and pictograms help the viewer see the risk in context and facilitate accurate judgements of probability [48,49]. Again, this format will be animated, highlighting each affected heart in turn, to account for the range of numbers affected in the risk category. A metonym format will be used in intervention group 2. This will depict the seriousness of an emergency admission for a myocardial infarction. This has been chosen as heart disease is generally associated with having a myocardial infarction [50]. An image demonstrating healthy longevity will be shown to those in the low risk category; those at moderate risk will be shown an ambulance traveling towards a person's house, and a person being defibrillated will be shown to the high risk category.

To assess changes in emotional affect and worry, all respondents will have these measured at baseline during the risk assessment. Those in the bar graph and pre-intervention questionnaire group (control group 1) will also complete a partially parallel version of the post-intervention questionnaire. This is to address the Hawthorne effect of the four groups, and compare those who are asked to think about their cardiovascular risk and their prior intentions to reduce this, against those who are not. However, to keep the total number of items to a minimum, the focus is on reducing overall cardiovascular risk, instead of specific behaviours that lead to risk reduction. All respondents will view the risk in the format that they have been randomly assigned to and complete the post-intervention questionnaire.

There will be two main comparisons:

1. (a) Bar graph only v. Pictogram

(b) Bar graph only v. Metonym.

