*(ii) Understanding *- Items specific to the understanding of cardiovascular risk information have been developed and will be piloted, as no suitable validated scale currently exists. These comprise absolute probability perception e.g. *'What are your chances of having heart disease in the next 10 years?' *with three pre-defined response options (low, moderate, high*)*; subjective understanding of the risk information e.g. '*What should someone in your risk category do to reduce their risk of heart disease*?' with 3 pre-defined response options (do nothing to reduce their risk, try and do a little bit to reduce their risk, do as much as they can to reduce their risk); and confidence in understanding e.g. '*How confident are you that you have understood the risk information given to you?' *with a 7 point Likert Scale to indicate level of confidence in understanding.

*(iii) Emotional affect after viewing cardiovascular risk - *The Positive and Negative Affect Schedule- Short Form (PANAS-SF) will be used [56]. This is a 10-item truncated version of the PANAS, which has been well validated and cited in over 2,000 scholarly papers [57]. It was felt that the original 20-items would be too time-consuming and cognitively demanding for respondents, possibly leading to high drop out rates. As this study is interested in respondents' changes of affect after viewing their risk output, a slight adaptation to the wording of the instructions and anchors/pole labels was made to the post-intervention scale, to make it more logical. An example of one item is: '*Thinking about yourself right now at this present moment, to what extent do you feel upset?' *with a 5-point Likert response scale anchored *'not at all' *to *'extremely'*.

*(iv) Worry about future heart disease - *one item will be used to measure this construct, in order to keep the total time needed to complete the questionnaires to a minimum. No previously developed and validated scale regarding worry about future risk of heart disease currently exists. Therefore, the item was developed using previously validated scales relating to other health conditions, such the Lerman Breast Cancer Worry Scale [58] as a guide. This item is '*After viewing your results, how worried do you feel about developing heart disease in the future?*' with '*very worried' *to '*not at all worried' *anchored on a 7-point Likert response scale.

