### viii) Analysis

The results will stored on a SQL database and fed back to the researcher via the server that hosts the website. The data will be stored on the shared drive which will be password protected and only accessible to the researcher. Data will be retrieved, coded and inputted into computer software. Microsoft Office Excel 2007 will be used for data manipulation and SPSS version 16 for the main data analyses.

The usual descriptive statistics will be presented to summarise baseline characteristics of the study sample. Continuous variables such as age and level of cardiovascular risk will be summarised using mean and SD and/or median and quartiles. Binary variables such as gender and whether the respondent requests an electronic copy of their risk output for their GP will be summarised by counts and proportions. Summary statistics will be obtained for the study population as a whole, and for the four randomised groups, without formal testing of statistical significance of any differences between them.

The main analyses of efficacy will relate to the primary outcome measures: intention to change behaviour, understanding of risk information, emotional affect and worry about future heart disease. Summary statistics for the four groups will be presented, as above. The four groups will first be compared on an equal footing using one-way ANOVA. The three selected pairwise contrasts between the specified groups, will then be constructed (e.g. bar graph only v. pictogram; bar graph only v. metonym; and bar graph and preintervention questionnaire v. bar graph only).

Several secondary analyses will be performed. For the bar graph and preintervention questionnaire group (control group 1), paired analyses will be used to assess serial changes in outcome measures between pre- and postintervention questionnaires.

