A multiple regression model will be used in a sub-group analysis to look for correlations between risk category on intention to change behaviour, understanding of risk and post worry about future heart disease outcomes, to see if responses are mediated by risk category. It will also be used to assess the correlational validity between intention to change behaviour, worry about future heart disease and understanding of risk information; to determine what level of worry increases intention to change behaviour and whether understanding also results in appropriate intentions. The subcomponents of the TPB (attitudes, perceived behavioural control and subjective norms) will also be examined, to see if they sufficiently predict intention to change behaviour (in order to test the efficacy of the model in predicting cardiovascular-related behaviour change).

The direct and indirect measures of intention to change behaviour will be correlated, to see whether those who report that they intend to change their behaviour actually take the opportunity to print out their risk output to take to their GP. Furthermore, a correlation between accurate understanding of risk information and confidence in understanding will be conducted. Lastly, Independent T-tests will compare baseline and post-intervention emotional affect and worry about future heart disease scores, to determine whether scores generally decrease after viewing a particular risk presentation format, or increase, demonstrating a possible negative impact.

For all analyses, point and interval estimates will be obtained, as well as p-values. In the event of substantial departure from Gaussian distributional form, transformation of scale and/or analogous non-parametric methods will be considered.

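### One secondary analysis reads a before-after change in affect or worry as the impact of the format shown, although every arm also learns its risk category and percentage between the two measurements

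*Protocol article*

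**What the plan says.** Three parts of the protocol article bear on the point.

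- **Timing and content of the intervention** (section v, Intervention and comparisons). For affect and worry, "all respondents will have these measured at baseline during the risk assessment", so the baseline precedes the result. After the risk assessment, "all respondents will be given their risk category (low, moderate or high) and the corresponding percentage figure". The randomised graphic accompanies that disclosure. It is what differs between arms, apart from the extra questionnaire in control group 1.
- **Instrument** (section vi, Outcome Assessment). For the short-form PANAS, "a slight adaptation to the wording of the instructions and anchors/pole labels was made to the post-intervention scale". The post-intervention worry item is also phrased in terms of having seen one's results.
- **Analysis** (section viii). Affect and worry are among the primary outcomes, for which "The four groups will first be compared on an equal footing using one-way ANOVA". Three pairwise contrasts follow, including bar graph only against pictogram and against metonym. Then, as the last of the secondary analyses, "Independent T-tests will compare baseline and post-intervention emotional affect and worry about future heart disease scores". The stated purpose is "to determine whether scores generally decrease after viewing a particular risk presentation format, or increase, demonstrating a possible negative impact".

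**The concern.** The secondary analysis sets a rule for judging a format: the direction of change over time among those who viewed it. It names no comparator arm. Yet viewing the graphic coincides with being told one's own 10-year risk, which can move affect and worry by itself in either direction. Answering the same questions a second time, in altered wording for affect, is a further source of change. All of these are shared by the four arms.

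At stake is a published statement that the pictogram or the metonym upset or reassured people when it did no more than the bar graph does. The Discussion intends the results for developers of risk tools, so such a statement could be acted on. The sign of the change would also depend on how many respondents turn out to be at low, moderate or high risk, which says nothing about the picture.

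**Working it through.** **The plan's own figure.** Section vii gives SD 1.5 for intention, a difference of 0.5, α = 0.05, 90% power and 200 per group. With a two-sided test, n = 2 × (1.960 + 1.282)² × 1.5² / 0.5² = 189.1, so 190 per group. At 200 per group the standard error of a difference is 1.5 × √(2/200) = 0.15, and power is Φ(0.5/0.15 − 1.96) = Φ(1.37) = 91.5%. The stated figure holds, and the point does not turn on it.

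**What each comparison estimates.** Let D be the effect of learning one's risk, M the effect of being measured again (including altered wording), and F the effect of the graphic in a given arm.

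- Before-after change in the pictogram arm: D + M + F(pictogram).
- Before-after change in the bar-graph-only arm: D + M + F(bar).
- Difference between these randomised arms: F(pictogram) − F(bar).

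Only the last line is free of D and M. A paired test estimates the same D + M + F as an independent test, with a different standard error, so it does not remove the problem.

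**Illustration with no format effect.** Inputs: 200 per arm (section vii). The remaining inputs are assumptions: SD 1.5 borrowed from intention, because the protocol gives none for worry or affect; a baseline–post correlation r of 0.3 to 0.7; and a common shift of 0.3 or 0.5 points.

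The independent test as written uses a standard error of 0.15 and so declares significance beyond 1.966 × 0.15 = 0.295. The mean change actually varies with standard error 1.5 × √(2(1 − r)) / √200. The chance of a significant shift in the assumed direction is Φ((shift − 0.295) / that standard error).

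| r | True SE of mean change | Shift 0.3 | Shift 0.5 |
|---|---|---|---|
| 0.3 | 0.125 | 52% | 95% |
| 0.5 | 0.106 | 52% | 97% |
| 0.7 | 0.082 | 52% | 99% |

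A simulation of 10,000 trials per setting agrees for the 0.5 shift: 94.7%, 97.4% and 99.5%. With a paired test the chances are 67%, 81% and 95% for a shift of 0.3, and 98% or more for 0.5. Comparing either the change or the post score between two randomised arms was significant in 4.5–5.5% of simulated trials across shifts of 0.25, 0.5 and 1.0, which is the nominal rate.

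**Precision of the alternatives** (same assumptions, for r = 0.3, 0.5, 0.7).

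- Difference in change between arms, √2 × the SE in the table: 0.177, 0.150, 0.116.
- Post score alone: 0.150 throughout.
- Post score adjusted for baseline, 0.15 × √(1 − r²): 0.143, 0.130, 0.107.

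**The case against.** The strongest reply is that the plan already holds the right comparison. Affect and worry are primary outcomes, and the main analysis contrasts pictogram and metonym with bar graph only between randomised arms. That stands, and it limits the point to one secondary analysis.

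A reader might go further and infer that the trial judges formats by before-after change, or that the primary objective "To analyse which format alters emotional affect" depends on it. The documents do not support this: the between-arm main analysis serves that objective. Nor do they plan to name a format by comparing significance from arm to arm.

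A second reply is that the sentence is hedged, speaking only of a possible impact, and that checking whether distress rises after a display is reasonable description. It is, provided the rise is not credited to the display.

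A third is that independent t-tests are a between-group method, so a comparison of change between formats may have been meant. The literal text has the tests compare baseline with post-intervention scores, which favours the before-after reading. If the other was meant, the sentence should say so. Using an independent test on scores from the same respondents is a separate fault.

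Finally, the illustration rests on a borrowed SD and an assumed shift. If relief among low-risk respondents offsets worry among high-risk ones, the mean shift could be near zero or negative. It would therefore be wrong to conclude that every format will appear harmful. The argument needs only that any common shift, up or down, would be attributed to the format.

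**Conclusion.** The point holds for the inference attached to the last secondary analysis and no further. A rise or fall in affect or worry within a format cannot show that format's impact, because disclosure of risk and re-measurement are common to all arms. This follows from the design and needs no numerical assumption.

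The numbers only show how easily a shared shift would reach significance: about 52% of trials at 0.3 points and 95–99% at 0.5 with the test as written, against about 5% between arms. They assume SD 1.5, r of 0.3 to 0.7 and no format effect. The real size and sign of the shift are unknown.

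The primary comparison, the sample size and the data collection are unaffected. The correction is still worthwhile because the baseline affect and worry scores, collected in all arms, are given no stated role in the between-arm contrasts.

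**What to change.** Reword the last secondary analysis in section viii so that any statement about a format's positive or negative impact rests on the randomised contrast of pictogram, or metonym, with bar graph only. Use the post-intervention score adjusted for the baseline already collected, or the difference in change. Adjustment is preferable: under the assumptions above it is the more precise of the two, and it does not require subtracting affect scores taken with different wording and anchors. Keep before-after change within each arm as a description of the overall effect of receiving risk information, and say that it is not evidence about the graphic.

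The cost is analysis wording only, with no new data. An unadjusted contrast of change between arms has about 1.4 times the standard error of a within-arm change (√2, with equal arms), which is what attribution to the format requires.

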## Discussion

This protocol provides a detailed description of a RCT designed to compare different graphical cardiovascular risk presentation formats and evaluate their effects on patient-related outcomes. The findings will inform developers of cardiovascular risk prediction tools and risk reduction interventions, providing insight into which format is most effective in encouraging behaviour change to reduce cardiovascular risk.

As far as we are aware, this will be the first RCT to assess different cardiovascular risk graphical presentation formats using actual risk assessment, rather than relying on hypothetical risk scenarios. However, a couple of limitations should be acknowledged. Firstly, a meaningful response rate will not be able to be calculated, but web-logs will give information on response trends (such as those who do not complete the study). Secondly, there is sample bias, as this study uses a self-selecting sample and is restricted to computer literature individuals. Further possible biases will be explored in the event that no difference between the risk presentation formats occurs; this is to avoid under-estimation of their effects.

Lastly, we are only able to provide respondents with a rudimentary estimation of their future 10-year risk of having a CHD event, and present them with a risk category that has wide confidence intervals and a high level of uncertainty. This is due to the use of an algorithm that uses non laboratory, self-reported information [47]; which has been chosen to increase the feasibly of data collection. Nonetheless, this will be an adequate starting point for individuals who have not thought about visiting their GP for a clinical assessment before and may not know that they are at risk.

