### iv) Recruitment

Respondents will be invited to take part in the study using a number of methods. In order of implementation and preference, these methods are: emails to educational institutions, co-operation with large organisations where the workforce has access to a computer; social networking websites (such as *Facebook) *and advertisements in local newspapers. The study will also be advertised on posters and pocket sized cards.

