### vii) Sample size calculation

For simplicity, the sample size calculation is based on a comparison of means, though the analysis will recognise the ordinal nature of the data. It is hard to speculate on the difference between the groups and so the sample size is based on comparing 2 groups on the primary outcome measure which is intention to change behaviour; this will give a group size which will be used for all the groups. Recruitment will continue until 800 respondents (200 in each group) have completed the trial. The likely uptake rate is unknown and a number of the suggested recruitment methods may be needed. Based on a study that used a similar Likert Scale scoring system for a different risk context [59], the scores on intention to change behaviour within a group should have an SD of about 1.5. The total sample size in each group of 200 would then be sufficient to detect a difference of 0.5 point between two groups, with 90% power and significance value of *α = *0.05.

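### Further biases are to be explored only after a null result, and only against under-estimation, although counting completers to 200 per arm leaves the contrasts open to format-related dropout in either direction

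*Protocol article*

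**What the plan says.** The Discussion of the protocol article lists limitations. It first notes that no meaningful response rate can be calculated but that "web-logs will give information on response trends (such as those who do not complete the study"), then that the sample is self-selected. It continues: "Further possible biases will be explored in the event that no difference between the risk presentation formats occurs", and gives the reason: "this is to avoid under-estimation of their effects".

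Three other places bear on this:

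- **Intervention and comparisons.** After consent and the eligibility check, "The computer will then randomise the respondent into one of the four arms, ensuring allocation concealment". The risk assessment, the format and the post-intervention questionnaire all come later. The same section says: "To assess changes in emotional affect and worry, all respondents will have these measured at baseline during the risk assessment".
- **Sample size calculation.** "Recruitment will continue until 800 respondents (200 in each group) have completed the trial".
- **Aims and Objectives.** One secondary objective is: "To evaluate the use of the internet-provided risk formatter (process evaluation), including analysis of web-logs". It does not depend on the result.

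**The concern.** Whether bias is looked for should not depend on how the trial comes out. Under the stated rule a null result gets a second look aimed at recovering an effect. No matching look is stated for a positive result, although bias can create or inflate a difference as easily as hide one.

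The design offers a concrete route for such bias. Allocation precedes exposure, so a respondent can leave because of what the arm showed or asked. Those who leave do not count towards the target and are in effect replaced. That preserves power but does not make the completers of different arms comparable.

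The arms differ in ways that could matter. Only control group 1 answers an extra questionnaire, and only the metonym arm shows high-risk respondents a person being defibrillated. The Background itself says that too much worry can lead people to ignore or distort information. At stake is the reading of the pairwise contrasts on the primary outcomes.

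**Working it through.** **1. The plan's own figure.** Inputs from the Sample size calculation: difference 0.5, SD 1.5, power 90%, α 0.05 (two-sided is assumed because sidedness is not stated).

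- n per group = 2 × (1.960 + 1.282)² × 1.5² / 0.5² ≈ 189.1, rounded up to 190.
- With 200 per group the standard error is 1.5 × √(2/200) = 0.15. Power = Φ(0.5/0.15 − 1.960) = Φ(1.373) ≈ 91.5%.

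So 200 is sufficient, as stated. An observed difference of 1.960 × 0.15 ≈ 0.29 is already significant.

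**2. What dropout in one arm could do.** The document gives no dropout rate, so the rates below are assumptions. Suppose:

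- the true difference is zero;
- a fraction d of one arm leaves in excess of the other;
- the tendency to stay has correlation ρ with the intention score (normal model, SD 1.5);
- each arm still reaches 200 completers.

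With c the d-quantile of the standard normal distribution:

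- λ = φ(c)/(1 − d)
- shift of the completers' mean = 1.5 × ρ × λ
- variance of completers relative to 1.5²: v = 1 + ρ²(cλ − λ²)
- standard error of the contrast = 1.5 × √((1 + v)/200)
- type I error = probability that the contrast exceeds ±1.960 standard errors

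Worked case, d = 20% and ρ = 0.5: c = −0.842 and λ = 0.280/0.8 = 0.350, so the shift is 1.5 × 0.5 × 0.350 = 0.262. Then v = 1 + 0.25 × (−0.295 − 0.122) = 0.896 and the standard error is 1.5 × √(1.896/200) = 0.146. The shift is 1.80 standard errors, and the type I error is Φ(1.80 − 1.96) ≈ 0.435.

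| d | ρ | Shift (points) | Type I error | Randomised for 200 completers |
|---|---|---|---|---|
| 5% | 0.3 | 0.049 | 0.062 | 211 |
| 5% | 0.5 | 0.081 | 0.085 | 211 |
| 10% | 0.1 | 0.029 | 0.054 | 223 |
| 10% | 0.3 | 0.088 | 0.091 | 223 |
| 10% | 0.5 | 0.146 | 0.168 | 223 |
| 20% | 0.1 | 0.052 | 0.064 | 250 |
| 20% | 0.3 | 0.157 | 0.185 | 250 |
| 20% | 0.5 | 0.262 | 0.435 | 250 |

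With ρ = 0 the error stays at 5% whatever the dropout. With ρ = 1, where exactly the extreme tail leaves, the shift is 0.292 at 10% and 0.525 at 20%. Those are upper bounds.

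**3. Direction.** The shift takes its sign from who leaves. Loss of the least willing raises the arm's mean and can produce a false difference in its favour. Loss of the most worried lowers its worry score. The Background says worry predicts intention, so that loss could also lower intention and mask a real effect. A check triggered only by a null result covers the second case and not the first.

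**The case against.** The strongest reply turns on the wording. The rule concerns further biases, beyond those just named. Non-completion is the first one named, and its web-log information does not depend on the result. A reader might infer that dropout behind a positive result would never be checked; the document does not support that, because web-log analysis is planned in any event. What remains is that the logs are described as showing response trends and completion times, with no comparison by arm and no link to interpreting a positive contrast.

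A second reply is that attrition analyses are commonly left to an SAP or full protocol. That stands as far as it goes: their absence from an article is no finding. But the result-dependent trigger is a stated rule, and an unseen document that adds checks would still leave this sentence to be changed.

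Other stronger readings also fail:

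- **Arms topped up one by one, with later recruits from other sources concentrated in high-dropout arms.** The recruitment sources are sequential ("In order of implementation and preference, these methods are: emails to educational institutions", then others), but the article does not say that arms close separately, and it says only that several methods may be needed.
- **Control group 1 loses people to a long questionnaire.** Nothing says it is long; items were deliberately kept few. That arm is also in neither format contrast, so its dropout affects the Hawthorne comparison and the four-group ANOVA.
- **The bias can only favour a format effect.** It can go either way. The ANOVA and contrasts are fixed; only the scrutiny is one-sided.
- **High dropout in the metonym arm is to be expected.** The defibrillation image goes only to its high-risk members, whose share is not given.

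**Conclusion.** The point holds in this form: the Discussion fixes a result-dependent, one-directional rule for exploring further biases. The design allows format-related dropout to distort a contrast either way, and no by-arm check of completion is tied to a positive finding.

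The size cannot be settled from the document. It depends on excess dropout in one arm and on how strongly leaving relates to intention. With 10-20% excess dropout and a correlation of 0.3-0.5, the shift is about 0.09-0.26 points, or 18-52% of the 0.5-point target difference (0.09/0.5 to 0.26/0.5), and type I error is about 9-43%. With 5% dropout it is at most about 8.5% for correlations up to 0.5, and with a correlation of 0.1 it is at most about 6.4% for dropout up to 20%. If both arms lose similar people at similar rates, the shifts largely cancel.

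The figures use the SD for intention and should not be carried over to worry, for which no SD is given. The change should be made, but this is no evidence that the trial is biased.

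**What to change.** 1. Reword the sentence in the Discussion so that possible biases are explored whatever the result and in both directions, over-estimation as well as under-estimation.
2. Report the numbers randomised, shown the format and completed, by arm and risk category.
3. Add one sensitivity analysis of the pairwise contrasts, weighted or imputed on risk category and baseline worry and affect, all of which come from the risk assessment. It corrects only for dropout that these variables explain, and this should be said when it is reported.

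The cost is a wording change and a small amount of extra analysis. The responses of non-completers up to the point of exit must be stored; the article does not say whether they are. The randomisation point, the closing of arms and the target of 200 per group need not change for this.
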